### Primary outcome measures

C-ACT scores will be analysed in a multilevel repeated measures regression model, which incorporates the C-ACT scores for all measurements, including the baseline measurement. This method takes into account within-patient correlation by modelling the covariance structures of the residuals per measurement. Several structures will be considered, starting with the unstructured covariance structure.

The differences in C-ACT scores between the two groups will be modelled by the interaction of treatment and measurement after baseline, assuming that any difference in C-ACT at baseline is due to chance. Additional variables will be considered for inclusion in the regression model if they are substantially different at baseline or if they are expected to be predictive of drop-out at a later stage.

Furthermore, a subgroup analysis will be conducted in which the total sample is divided into three groups according to their baseline characteristics; a group with insufficient asthma control (undertreated children), a group with sufficient asthma control and continuous ICS use (possible overtreated children) use and a group with the remaining children.

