### Randomisation

The participating health centres (ie, one or more collaborating GP practices) will be the units of randomisation. They will be randomly assigned to either the intervention or control group (‘usual care’) with a 1:1 allocation as per a computer-generated stratified randomisation schedule. When a practice nurse works for several GP practices, all these practices will be part of the same cluster and randomised as one group. When a health centre consists of several GP practices with their own practice nurse, this health centre will also be considered as one cluster. When two practice nurses are working in one GP practice (not separated), this GP practice or health centre will be randomised as one cluster. When patients are eligible for inclusion in the trial and provide informed consent, a researcher will conduct the randomisation using an online randomisation programme and the patients will be informed in which treatment arm their GP practice is randomised. The cluster randomisation is conducted within 8 weeks after inclusion of the first patient of that GP practice into the present study. All subsequent patients of the same cluster will receive the same intervention.

Stratification will be based on the size of the GP practice and the number of years of experience of the GP. For example, GP practices in a single health centre (the same postal code) will be randomised in a stratified randomisation of four groups and, therefore, evenly distributed to the intervention and the control arm to minimise differences in baseline characteristics of the patients. A block randomisation with varying blocks (ie, 2–6 blocks) will be used to equally balance both groups. The sequence is kept secret from all researchers involved in the study.

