### Sample size

To our knowledge, no previous study has determined the minimally important difference (MID) for the C-ACT for children with asthma in primary care. Therefore, we decided to extrapolate the C-ACT score of a previous study (that included 166 children aged 6–11 years with asthma from secondary care)^26^ to our sample size calculation.^23^

Considering an MID of 2, a mean C-ACT score of 19.8 and with a SD of 4.1,^26^ a sample size of 126 children will be needed to achieve a power of 80% with an alpha of 5%. Using an intracluster correlation of 0.04^31^ and inflating the sample size with 15% to take into account expected loss to follow-up, the sample size has to increase to 180 patients.

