### Secondary outcome measures

The numbers of exacerbations will be analysed in Poisson-type regression models, with the time spent in the study as offset, thus adjusting for potential loss to follow-up. The other secondary outcome measures, that is, generic quality of life (measured by CHU9D and EQ-5D), disease-specific quality of life (PAQLQ), satisfaction and 3-monthly costs will be analysed in separate multilevel regression models. The probability of achieving asthma control at any moment in time will be analysed in a multilevel logistic regression model. Asthma control is defined as a C-ACT score of 20 or better.

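### The primary model does not name the randomised cluster or the stratification factors, and it lets observed baseline imbalance choose covariates

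*Protocol article*

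**What the plan says.** Under Randomisation, whole clusters are allocated 1:1, and "Stratification will be based on the size of the GP practice and the number of years of experience of the GP". Under Sample size, clustering is allowed for: "Using an intracluster correlation of 0.04".

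Under Analyses, Primary outcome measures, C-ACT is analysed in a multilevel repeated measures regression that includes the baseline score. The levels are not listed. The dependence it handles is described in one sentence: "This method takes into account within-patient correlation by modelling the covariance structures of the residuals per measurement". The Missing data section likewise refers only to correlation between a child's own observations.

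On covariates, the same section states: "Additional variables will be considered for inclusion in the regression model if they are substantially different at baseline". The sentence then adds a second route, for variables expected to predict drop-out. It gives neither a list nor a threshold.

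For exacerbations: "The numbers of exacerbations will be analysed in Poisson-type regression models, with the time spent in the study as offset". The other secondary outcomes are given multilevel models; this sentence does not use that word.

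**The concern.** The design and the sample size both recognise that children in one cluster resemble each other. The analysis text describes the within-child covariance in some detail, yet never mentions the level that was randomised. If that level is left out of the fitted model, the standard error of the treatment effect is too small and the primary test exceeds its nominal 5%.

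Two further matters sit beside this and work differently. The stratification factors constrain the allocation but are absent from the model, which gives up precision. And admitting a covariate because it happens to differ between arms means the primary model cannot be written down until the data are seen.

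**Working it through.** **Inputs.** From Sample size: difference 2, SD 4.1, alpha 5%, power 80%, ICC 0.04, loss 15%, final N 180. Two-sided testing is assumed, since the article does not state it. The number of clusters is not stated either. The Setting section gives 13 health centres and at least 14 further practices, so about 27 is used as an assumption.

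**1. The plan's own figure.** Per arm, n = 2(1.96 + 0.842)² × 4.1² / 2² = 65.97, so 66 per arm and 132 in total. The plan states 126. SD 4.0 gives 62.8, so 63 per arm and 126. This mismatch is a separate matter and does not affect what follows.

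**2. Cluster size implied by 180.** The step from 126 to 180 fixes the design effect (DE), and DE = 1 + (m − 1) × 0.04 then gives the mean cluster size m.
- Loss as division: 126/0.85 = 148.2; 180/148.2 = 1.214; m = 6.4.
- Loss as multiplication: 126 × 1.15 = 144.9; 180/144.9 = 1.242; m = 7.1.

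With 27 clusters, 180/27 = 6.7 children recruited and 153/27 = 5.7 completing (153 = 180 × 0.85). The inflation is therefore plausible, and the sample size does allow for clustering.

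**3. Consequence if clusters are left out.** The standard error is multiplied by 1/√DE, and the actual two-sided error is 2[1 − Φ(1.96/√DE)].

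| m | DE | SE too small by | Actual error |
|---|---|---|---|
| 5.7 | 1.187 | 8% | 7.2% |
| 6.4 | 1.214 | 9% | 7.5% |
| 6.7 | 1.227 | 10% | 7.7% |
| 7.1 | 1.242 | 10% | 7.9% |

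Simulation (26 clusters, mean size 6, ICC 0.04, 20,000 runs) gives 7.0% with equal clusters and 8.4% with unequal ones (coefficient of variation 0.6, assumed). An analysis of cluster means on the same data gives 4.6 to 4.7%. Over assumed ICCs of 0.01 to 0.10 and m of 5 to 10, the formula gives 5.5% to 15.5%.

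**4. Averaging over visits, and the baseline score.** Take a within-child correlation r = 0.5 and a cluster effect constant over time (both assumed), with single-visit variance 1.
- Mean of the four follow-up visits, ignoring baseline: variance 0.5 + 0.5/4 = 0.625; ICC = 0.04/0.625 = 0.064; error 8.5% at m = 5.7 and 9.3% at m = 6.7.
- Using baseline, with the cluster effect also present there: ICC = 0.04 × (1 − 0.5)² / (0.625 − 0.25) = 0.027; DE 1.12 to 1.15; error 6.5% at m = 5.7, 6.8% at m = 6.7 and 6.9% at m = 7.1.

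The planned model uses the baseline score, so the second line is the closer one. For m of 5.7 to 6.7, r from 0.3 to 0.7 moves it between 5.7% and 8.4%.

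**5. The covariate rule.** No arithmetic applies. The section first treats any baseline difference in C-ACT as due to chance. Its next sentence lets a baseline difference in any other variable count towards inclusion. In a randomised comparison those differences are chance too. Their size says nothing about whether the variable predicts C-ACT, which is what makes adjustment worthwhile.

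**The case against.** The strongest reply is the word *multilevel*. Within-child correlation is already handled by the residual covariance, so a further level would naturally be the cluster, in an article that presents a cluster design throughout. This stands to the extent that omission is not shown. A reader might infer that the plan drops the clusters and that its standard errors are too small; the text supports neither as a fact. But visits within children are themselves two levels, so the word does not settle the matter.

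A second reply is that an article condenses, and that random-effect structure, degrees of freedom and covariate lists belong in an analysis plan. That is fair for silence alone. Here, however, the article sets out the dependence structure and stops short of the randomised level, and the imbalance criterion is a stated choice rather than a gap.

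Three other strong readings also fail.
- Covariates do not enter solely on imbalance: expected drop-out predictors are a second route, and the wording is that variables will be considered.
- Missing stratification factors do not make standard errors too small; leaving them out is usually conservative.
- The exacerbation model is not shown to ignore overdispersion, because Poisson-type leaves room for it. That is only a clarification.

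**Conclusion.** The point holds as a failure to specify. The primary analysis text covers within-child correlation and does not identify the randomised cluster, although allocation and sample size both depend on it. If clusters were left out, the 5% test would run at roughly 7 to 8% at the plan's ICC with 6 to 7 children per cluster, or about 6.5 to 7% if baseline C-ACT carries part of the cluster effect. These figures rest on the ICC of 0.04, an assumed cluster number and size, and, for the lower range, r = 0.5 and a stable cluster effect. An error near 9% might be inferred from averaging four visits, but that calculation ignores the baseline score the model uses.

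The absent stratification factors cost precision only. The imbalance criterion is a separate, unconditional weakness: it makes the primary model partly data-driven, and its effect on the estimate cannot be sized from the article.

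**What to change.** In Analyses, Primary outcome measures:

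- State a random intercept for the randomised cluster in addition to the within-child covariance, with a small-sample degrees-of-freedom correction such as Kenward-Roger or Satterthwaite.
- Define that cluster once. The Abstract names practice nurses as the randomised units, whereas Randomisation names health centres; reconcile the two.
- Include practice size and GP experience, as used in the stratification, as fixed effects.
- Delete the baseline-imbalance criterion. List the prognostic or drop-out-predictive covariates before any data are seen.

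In Secondary outcome measures, carry the same cluster effect into the exacerbation model, keep the time offset, and say how overdispersion will be handled.

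The changes are to wording. Practice membership and the stratification factors are already needed for the randomisation, so no new data are required. The cost is slightly wider confidence intervals.

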### Secondary outcome measurements

Differences in C-ACT scores within a study subject (subjects in the non-randomised group of protocolled nurse led care), will be estimated with a paired Z-test or paired t-test. Besides we will determine differences in outcome between the randomised and non-randomised protocolled nurse-led care samples and the usual care group by using unpaired t-test in case of normally distributed values and Mann-Whitney U test in case of non-normally distributed values. For categorical outcomes, we will use Chi-square test for statistical analyses.

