## Methods/design

### Design

The aim is to conduct a cluster RCT with a follow-up of 18 months. Recruited practice nurses (or groups of practice nurses) representing one cluster will be randomised into one of the two arms: (1) protocolled nurse-led care or (2) ‘usual care’ by the GP. During the study, a number of potential participating GPs were already intending to start protocolled nurse-led care for children with asthma in their practice. Because of this reason, we decided to enable these health centres to participate in the non-randomised part of the trial. This new sample was added after the study started and the change was approved by the ethics committee. All measurements and study procedures (except for the randomisation) will be identical to the randomised group of patients. Figure 1 is a flowchart of the study design.

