### Study procedures (non-randomised group)

Besides the cluster randomised group of children we will include a non-randomised group of children in this trial. These children will be recruited in health centres who intend to start protocolled nurse-led care for children with asthma in their practice. Practice nurses of the non-randomised participating GP practices will attend the same training on protocolled asthma care. All eligible children who receive protocolled nurse-led care will be invited to participate in the non-randomised part of this trial. They will be invited by their GP with a slightly adjusted invitation letter, the other study procedures will be identical.

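### The self-selected nurse-led sample is compared with the randomised arms by tests that ignore clustering and confounding

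*Protocol article*

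**What the plan says.** The Design section explains that a non-randomised part was added after the study had started, because "a number of potential participating GPs were already intending to start protocolled nurse-led care for children with asthma in their practice". The section Study procedures (non-randomised group) confirms the source: "These children will be recruited in health centres who intend to start protocolled nurse-led care for children with asthma in their practice". Children in those centres who receive nurse-led care are invited, with a slightly different letter.

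The analysis of this sample is in Secondary outcome measurements. Within-child differences in C-ACT in the non-randomised group "will be estimated with a paired Z-test or paired t-test". The plan then examines "differences in outcome between the randomised and non-randomised protocolled nurse-led care samples and the usual care group", and does so "by using unpaired t-test in case of normally distributed values and Mann-Whitney U test in case of non-normally distributed values". It adds: "For categorical outcomes, we will use Chi-square test for statistical analyses".

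Other sections treat the data differently. The Sample size section inflates for an intracluster correlation of 0.04. Under Analyses, Primary outcome measures specifies a multilevel repeated measures model for the difference between two groups, treats baseline C-ACT differences as chance, and allows extra covariates. In the section Secondary outcome measures that follows Missing data, quality of life, satisfaction and costs "will be analysed in separate multilevel regression models", and asthma control gets a multilevel logistic model.

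**The concern.** The added sample differs from the randomised arms by more than treatment. Its practices chose nurse-led care, it joined later, and its children are invited as recipients of that care. In the randomised part, Study procedures describes consent before allocation. An unadjusted contrast with usual care therefore mixes any effect of nurse-led care with differences between practices, children and calendar periods. The direction of that bias cannot be known in advance.

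Clustering is a separate fault. Children of one practice are not independent. A t-test, Mann-Whitney U test or chi-square test treats them as if they were, so p-values are too small and intervals too narrow. This does not shift the estimate; confounding does.

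The before-after test has no comparator, so ageing, season and regression to the mean all count towards the change it detects.

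The sentence naming the three groups also allows a reading in which randomised nurse-led care is tested against usual care by t-test or chi-square, beside the multilevel models given elsewhere for the same outcomes. The plan does not say which would take precedence. According to Ethics and dissemination, results may go straight into guideline revisions, so the status of each comparison should be clear.

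**Working it through.** **Inputs from the Sample size section:** ICC 0.04, SD 4.1, minimally important difference 2, 126 children before inflation, 15% loss, 180 in total. Alpha is 5%, taken as two-sided.

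**Assumed, because the article does not give them:** cluster size m, the size of the non-randomised group, the selection shift, and the drift and within-child correlation for the paired test.

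**1. The plan's own inflation.** With DE = 1 + (m − 1) × 0.04 and m = 7, DE = 1.24 and 126 × 1.24 × 1.15 = 179.7, which matches 180. Dividing by 0.85 instead of multiplying by 1.15 implies m of about 6.4. So 6 to 7 children per cluster fits the plan's arithmetic, though the number is not stated and non-randomised clusters may differ. (The 126 itself is not reproduced: the usual formula gives 66 per arm, or 132. That is a separate matter and plays no part here.)

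**2. Clustering ignored, no confounding, no effect.** Actual alpha = 2 × [1 − Φ(1.96/√DE)].

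| m | DE at ICC 0.04 | Actual alpha |
|---|---|---|
| 5 | 1.16 | 6.9% |
| 7 | 1.24 | 7.8% |
| 10 | 1.36 | 9.3% |
| 20 | 1.76 | 14.0% |

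For m = 7: 1.96/√1.24 = 1.760, two-sided tail 7.8%. A simulation of t-tests (20,000 runs, 9 clusters of 7 per group) gave 7.9%. At m = 7, an ICC of 0.01 gives 5.7% and an ICC of 0.10 gives 12.1%.

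**3. Selection shift b with no treatment effect.** SE = 4.1 × √(2/n) with n children per group. P(significant) = 1 − Φ[(1.96 − b/SE)/√1.24] + Φ[(−1.96 − b/SE)/√1.24].

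| b (C-ACT points) | n = 60 per group | n = 90 per group |
|---|---|---|
| 0.5 | 13% | 16% |
| 1 | 29% | 39% |
| 2 | 74% | 88% |

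For b = 1 and n = 60: SE = 0.749, b/SE = 1.336, (1.96 − 1.336)/1.114 = 0.560, upper tail 28.8%; the lower tail adds about 0.1%. One point is 1/4.1 = 0.24 SD and half the minimally important difference.

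**4. Uncontrolled paired test with no treatment effect.** For an assumed 1-point drift and correlation 0.5, SE = 4.1 × √(2 × 0.5)/√n, and P = Φ(1/SE − 1.96). This gives 34% (n = 40), 47% (n = 60) and 64% (n = 90). A 0.5-point drift gives 12%, 16% and 21%.

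**The case against.** The strongest reply is that this is a supplementary analysis. The sample is called non-randomised wherever it appears, and neither the aim nor the sample size rests on it. The primary comparison uses a multilevel model of two groups. That stands, and it limits how serious the point is.

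Several stronger readings are tempting but not supported:

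- A reader might infer that these contrasts are meant to be read as treatment effects. The article makes no such claim. It only lacks a caveat or an exploratory label.
- A reader might infer that the randomised contrast will be tested twice. The sentence permits this but does not establish it. Spirometry and medication use have no named regression model, so the simple tests may be meant for them.
- A reader might infer that non-randomised children enter the subgroup analysis, since "a subgroup analysis will be conducted in which the total sample is divided into three groups". That phrase follows directly on a paragraph about two groups, and their inclusion is not stated.
- The paired test might be taken as a comparison with the randomised arms. It is confined to the non-randomised group.
- Nothing says that the unpaired tests are run visit by visit; the article speaks only of differences in outcome.

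The reply does not reach the core. The tests are named, so this is not a detail left to an analysis plan, and none of the named tests can carry a cluster effect or a covariate.

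**Conclusion.** The point holds for the comparisons that involve the non-randomised sample. The stated tests ignore the clustering that the protocol itself assumes, and they leave self-selection and later entry unadjusted. Clustering alone raises a 5% test to about 7% to 9% at ICC 0.04, if clusters hold 5 to 10 children. A selection difference of 0.5 to 1 point would give a significant result without any treatment effect in about 13% to 39% of cases, for 60 to 90 children per group. These figures illustrate scale; the shift and the group sizes are not in the article.

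The primary randomised result is sound in this respect provided it uses randomised clusters only, which the text should say. Whether the simple tests also apply to the randomised contrast is an ambiguity to be cleared up, not a demonstrated double test. This should be fixed before analysis, but it does not undermine the trial's main inference.

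**What to change.** - Replace the t-test, Mann-Whitney U and chi-square plan with a multilevel model with a cluster random effect and three groups: randomised nurse-led, usual care and non-randomised nurse-led. The primary model cannot be reused unchanged, because treating baseline C-ACT differences as chance is justified only by randomisation. Give the non-randomised group its own baseline mean, or adjust follow-up C-ACT for baseline C-ACT.
- Adjust for age, ICS use, practice size, GP experience and calendar period.
- Label these comparisons observational and exploratory, report estimates with confidence intervals, and do not pool them with the randomised effect.
- Report the before-after change descriptively, beside the usual care change over the same period.
- State that the randomised comparison and the subgroup analysis use randomised clusters only, and that the multilevel models are the only tests of the randomised contrast for the outcomes they cover. Say which analysis applies to spirometry and medication use.

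The cost is mostly wording. No new measurements on children are needed. Practice size and GP experience already serve as stratification factors and would also have to be recorded for the non-randomised practices. Intervals for the added sample will be wider and the claim weaker, and adjustment cannot remove unmeasured differences between practices.

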### Missing data

The multilevel regression model also deals with missing observations of the outcome measure by exploiting the fact that observations within patients are correlated, if the missingness occurs completely at random or at random (conditional on the observed data in the model). This allows unbiased estimation of regression coefficients and to make optimal use of all available data, even when some measurements are missing.^32^ Dropouts or missing visits will be reviewed to identify possible informative missingness.

